**Metabolic profile:**

• **Hyperinsulineamic euglyceamic clamp:** Intravenous infusion of rapid-acting insulin (Actrapid, Novo Nordisk A/S, DK) 0.6 mU/kg TBW/min, while continuous intravenous infusion of a 20% glucose solution is adjusted in order to keep plasma glucose ~ 5 mM. Measuring blood glucose every 5-10 min and corresponding adjusting the glucose infusion rate ensure the level of glucose. The amount of infused glucose (M-value) is a measure of insulin sensitivity.

• **Carbamidtracer:** A bolus of ^13^C-urea (390.6 mg) followed by constant infusion of ^13^C-urea (42 mg/hr) for 4 hours.

• **Glukosetracer:** A bolus ^3^H_3_-glucose (20 μCi) and followed by constant infusion (0.20 μC/min) for 6 hours.

• **Palmitattracer:** FFA turnover is determined by Isotope dilution with 2 x 1 hour constant infusion of (9.10 -^3^H) palmitate (0.3 μCi/min giving a total of 18 x 2 μCi).

• **Amino acid tracers:** ^15^N-Tyrosine (0.3 mg/kg) and ^2^H_4_- Tyrosine (0.5 mg/kg) are given as a bolus. Then ^2^H_4_-Tyrosine (0.5 mg/kg/hr) is infused for 4 hours. ^15^N-Phenylalanine is given as a bolus (0.7 mg/kg) and then infused for 4 hours (0.7 mg/kg/hour).

• **Investigation of substrate metabolism in the forearm:** A plastic catheter is placed retrograde in a deep antecubital vein for collection of venous blood from the forearm muscle. On the opposite arm another catheter is placed antegrade in a vein on the back of the hand and in the antecubital vein. The hand is placed in a heated box whereby the blood is arterialized. Criteria for proper placement of the catheters are oxygen saturation below 70% for venous blood and more than 91% for arterialized blood. Before collecting blood, blood flow is measured with venous occlusion plethysmography. The blood flow to the hand is cut off with a cuff (250 mmHg) just before measuring blood flow and 1 minute before sampling from the vein. Arterial and venous blood is collected simultaneously.

• **Indirect calorimetric:** Indirect calorimetric (Oxycon Pro Care Fusion, Germany) is conduced 30 minutes prior to and at the end of the insulin clamp. This allows for calculations of total energy consumption, oxidative rates of glucose and fat, non-oxidative glucose turnover, and glucose output from the liver.

• **Biopsies:** Biopsies are taken one hour after the start of the metabolic profile and 30 minutes into the hyperinsulineamic clamp. *Fat Biopsies:* Subcutaneous fat is aspirated from the abdomen with a liposuction needle under local anesthesia and some of it is immediately frozen in liquid nitrogen. The remaining fat cells are purified by collagenase and stained with methylene blue for visualization of nukleii and cell membrane. Fat cell size is determined with a microscope and a camera is used to take pictures. *Muscle Biopsies:* A muscle biopsy is taken from the vastus lateralis with a Bergström needle. After 10-15 min. of local anesthesia (1% lidocaine), incision is made through skin and muscle fascia app. 15-20 cm above the knee. Muscle tissue is obtained and immediately frozen in liquid nitrogen or embedded in Tissue Tek and frozen. *Analyses:* Western Blot, PCR, immunohistochemical analysis, and intramuscular TG and glycogen.

• **Blood tests:** Blood samples are obtained every 20 minutes during the metabolic day. Total blood loss is around 320 ml. *Analysis:* Epo, total, free and bioactive IGF-I, IGFBP-1, glucose, insulin, C-peptide, free fatty acids, adiponectin, VLDL-TG, metabolites, glucagon, cortisol, catecholamines, albumin, phenylalanine enrichment, glucose specific activity, glycerol, lactate, ALT, alkaline phosphatase, bilirubin, pro-thrombin index, carbamid, ghrelin, and proteomics

• **VLDL studies:** These studies will be conducted before and after the 10 weeks intervention. 1 week in advance 60 ml of venous blood is sampled under sterile conditions. VLDL-TG will be insulated by ultracentrifugation (40000 g for 18 hours at 10 °C) and subsequent labeled with 20 μCi [1-^14^C] triolein. Sterility will be secured with cultivation before the sample is used for reinfusion. On the study day, the patient's own ex-vivo labeled VLDL-TG will be infused (autologous infusion) until steady state (4 hours). Blood samples will be obtained every 10 min over the last 30 min for determination of VLDL-TG SA and concentration.

• **VLDL-TG oxidation:** These studies will be performed before and after the 10 weeks intervention. VLDL-TG oxidation is measured by collecting expired air with hyamin-trapping for analysis of ^14^CO_2_, this is measured before the start of the metabolic day and 3 times during the last half an hour of the basal period.

- **MRI scanning:** MRI will be used to measure intrahepatic and intramyocellular lipid content. The liver and the tibialis anterior muscle will be scanned using a technique that combines MR imaging with localized proton MR spectroscopy with a voxel of 3x3x3cm, a 1.5T MR unit will be used together with a breath holding for 17 sec. Before entering the scanning room the subject will be asked about contra induced circumstances in relation to normal procedures for MRI. The subjects will be asked to remove any metal from pockets and remove jewelry. The subjects will be informed that MRI is a safe procedure without any risk of radiation. There will be a loud sound during the scanning, and the subjects will be given earplugs.

 
[figure not shown]

**Serum:** Serum will be collected before the study and on days 8, 15, 21, 36, 50, 64, 71, and 78 and 92 during the wash-out period. Hematological levels will be measured throughout the study, and treatment will be discontinued if the values are abnormal (Hematocrit >55%). The following will be measured; Hemoglobin, erythrocytes, iron, transferrin, ferritin, reticulocytes, haptoglobin, albumin, alkaline phosphatase, bilirubin, LDH, plasma hemoglobin, VLDL, FFA, ghrelin, and cholesterol. Proteomics analysis will be performed on blood samples taken before the study at baseline and on days 21, 71, and 92.

**Blood pressure measurements:** The subjects' blood pressure will be monitored throughout the study on the days when blood will be sampled. This is done to ensure that the treatment does not induce increased blood pressure.

Blood and tissue samples are used for analyses, and thereafter destroyed. A bio bank is therefore not created.

**SAFETY**

Before enrolling the participants in this trail a general medical examination will be performed.

Throughout the metabolic day a medical doctor and a laboratory technician will be present to make sure that the subjects are well and they will be able to measure vital parameters (blood pressure, pulse, blood sugar levels, and level of consciousness). Medical doctor [name] will perform all invasive procedures, and clinically responsible for the project is [name] [name].

Acute treatment with Epo is not associated with serious side effects, but may be associated with transient flu-like symptoms, which will disappear within a few hours. Prolonged treatment may be associated with increased risk of thrombosis, hypertension and iron deficiency. A protocol similar to the Epo treatment regimen used here, has previously been approved by the Ethics Committee of Copenhagen and Frederiksberg (Lundby et al., 2007; Thomsen et al., 2007; Borno et al. 2010; Juel et al. 2007; Lundby et al., 2008). Here an increase in hematocrit from 45% to 49% (P <0.05) was found (Juel et al., 2007). The risk of thrombosis is greater if the subjects also have hypertension. Subjects will therefore be included only if their blood pressure is normal (<135/85) and they will be excluded if their hematocrit exceeds 55% (present doping limit is 50%, and the limit for venesection 55%). To avoid iron deficiency, all subjects will be treated with 100 mg iron orally daily from 1 week before the start of the experiment until the end.

When obtaining the biopsies there is a very small risk of infection or bleeding in the tissue. The subjects are instructed to contact the person responsible for the project by symptoms such as redness, swelling, warmth, and soreness. Additionally mild pain from the site of the biopsy can be experienced within the first few days after the procedure has been performed, equivalent to a muscle rupture. There is a minimal risk of damaging the small nerves in the skin, causing numbness in a small area on the skin. Sense of touch is often back after a shorter or rarely longer period of time. We also have had two cases of damage to a motor nerve in the muscle, which has resulted in local muscle atrophy without affecting muscle function.

When placing the intravenous catheters for blood collection and infusion there is a very small risk of infection and subjects are instructed to contact the investigator by redness and soreness corresponding to the injection sites. There is a small risk of hypoglycemia during and after the hyperinsuliniemic euglyceamic clamp. The risk is minimized by insuring a stable blood glucose level before the subject leaves the research laboratory. In addition, subjects are informed about symptoms of hypoglycemia and the subjects are given tablets with grape sugar for intake in the case of hypoglycemia.

Serious event or serious adverse event: an event that at any dose results in death, is life threatening, requires hospitalization, or prolongation of existing hospitalization, results in persistent or significant disability. If a serious event/adverse event appears this is reported to the Medicines Agency and the Ethics Committee. In case of a severe event the trail is immediately stopped and treatment commenced. The subject is followed until symptom free and/or the condition is stable. All adverse reactions/incidents will also be indicated in the final report. Complications will be recorded in connection with aforementioned medical examination and the subject will be treated at the research laboratory, since the trial is conducted in a highly specialized hospital.

The total blood loss at each experimental day is about 320 ml. There is 10 weeks between each experimental day, thus, this blood loss is not expected to induce symptoms. For comparison, an ordinary blood donation is approx. 500 ml. In addition, around 5 ml of blood will be collected on days 8, 15, 21, 36, 50, 64, 71 during the treatment period and at days 78 and 92 during the washout period, in order to monitor the hematological values. In addition, the participants will give 60 ml of blood for labeling of VLDL 1 week before the last experimental day. Blood loss in total throughout the study will be approximately 850 ml during a 4 months period.

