**DESIGN**

• The experiment is a single-blind, randomized study.

• 40 subjects in total will be included and randomly assigned to one of the following groups (n = 10);

o Placebo treatment

o Placebo treatment + endurance training

o rHuEpo treatment

o rHuEpo treatment + endurance training

• Subjects are examined before and after 10 weeks of rHuEpo/placebo treatment, and after a 3 weeks washout period.

• EPO (Darbepoietin alpha) (~50IU/kg)/placebo (saline) is administered s.c. twice a week for the first 3 weeks at a dosage of 2x40 μg, and once a week from week 4-10 at a dosage of 20 μg.

• The endurance training will consist of 1 to 1.5 hours of cycling at 65-80% of VO_2_max, 3 times weekly. This was previously shown to cause an increase in maximum oxygen uptake (Midgley et al., 2006).

[figure not shown]

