**COMPENSATION**

Participants in the study will receive a compensation of 5500 DDK if they are allocated to the training group and 4500 DDK if part of the control group. This covers any inconvenience associated with the experiment. Transportation to and from the two experimental days will be covered but the subjects themself will pay the remaining. The compensation is taxable. If a participant is withdrawn from the study he will receive compensation in accordance to the participation time.

Layman description

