**METHODS**

**Medical examination:** Thorough objective medical examination will be made before the participants are enrolled in the study together with routine blood tests, a DEXA scan, and measurement of maximal oxygen uptake.

**Metabolic profile:** The experimental days take approx. 8 hours and will be conducted before treatment and again after 10 weeks of treatment. The subject should be fasting and lying in a bed.

o **Investigation of substrate metabolism in the forearm:** 3 thin plastic catheters are placed in 3 different veins for injection of various substances and to collect blood samples from. This allows for measurements of sugar, fat, and protein metabolism.

o **Biopsies:** Fat Biopsy: Fat biopsies are taken from underneath the skin on the stomach during local anesthesia. Muscle Biopsy: A muscle biopsy is taken from the thigh muscle during local anesthesia.

o **Blood tests:** Blood is sampled every 20 minutes during the experimental day. Total blood loss is approx. 320 ml.

o **Hyperinsulineamic euglyceamic clamp:** After approx. 4 hours we inject insulin for 2 hours to measure insulin sensitivity, while keeping the blood sugar levels constant.

o **Indirect calorimetric:** The expiration air is analyzed 30 min before and at the end of the insulin stimulation test. This allows us to calculate the total energy consumption, as well as sugar, protein, and fat turnover.

- **MR scanning**: MR will be used to access the lipid content in different tissues and organs. The subject will be lying down and be placed in the scanner, which is formed as a tube. The subjects will be informed about the MR scan, that it is a safe technique that does not induce any radiation. The will be a loud sound during the scanning and the subjects are offered earplugs.

**Blood tests:** Blood will be sampled before starting the treatment and on days 8, 15, 21, 36, 50, 64, 71 during the treatment, and on days 78 and 92 during the washout period. On these days, blood composition will be analyzed and if the values are abnormal, treatment will be discontinued. Proteomics analysis of blood samples will be performed on samples taken before the start of the study and on day 21, 71 and 92

**Blood pressure measurements:** Blood pressure will be measured on the same days as blood is collected.

Blood and tissue samples will be used for analyses immediately after termination of the study and hereafter destroyed. Thus, a bio bank is not created.

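### Within-group paired tests on the washout samples cannot separate Epo withdrawal from recovery after the roughly 320 ml blood loss at the end of treatment; marker inference should rest on the Epo-versus-placebo difference in change

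*Protocol*

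**What the plan says.** - **Blood loss.** SAFETY states: "The total blood loss at each experimental day is about 320 ml. There is 10 weeks between each experimental day". The only consequence it considers is symptoms: "There is 10 weeks between each experimental day, thus, this blood loss is not expected to induce symptoms".
- **Timing.** METHODS in the lay description says that the experimental days "will be conducted before treatment and again after 10 weeks of treatment". COMPENSATION confirms that there are two: "Transportation to and from the two experimental days will be covered". SAFETY adds a 60 ml draw for VLDL labelling one week before the last one.
- **Visit schedule.** DESIGN has four randomised groups of 10, two of them on placebo, under one schedule: "Subjects are examined before and after 10 weeks of rHuEpo/placebo treatment, and after a 3 weeks washout period". No group is exempted.
- **Primary endpoint.** The Serum paragraph of METHODS states: "Proteomics analysis will be performed on blood samples taken before the study at baseline and on days 21, 71, and 92". Days 78 and 92 are the washout samples, and only day 92 has proteomics.
- **Analysis.** STATISTICS plans group comparisons (t-test, ANOVA or non-parametric equivalents) and, within groups, paired t-tests or their equivalents, all at 0.05. It does not say which of the two carries the conclusion about a marker.

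**The concern.** The trial looks for serum markers that change with Epo exposure. BACKGROUND says that Epo is produced when oxygen tension is low and drives red cell formation, and it names hemoglobin mass and reticulocyte percentage as candidate markers of abuse. Removing red cells acts on the same system. A sizeable blood draw at the moment when treatment stops therefore adds a second stimulus to every washout sample, and the protocol does not discuss it as an influence on the markers.

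The weak place is the within-group paired test. A change from day 71 to day 92 in an Epo arm contains withdrawal of Epo plus recovery from the loss, and nothing inside that arm can divide the two. A significant change, or the absence of one, could be read as showing how long a marker persists after Epo is stopped, when part of it reflects the blood draw. The same applies to baseline versus day 21 if the first experimental day lies close to the first dose.

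**Working it through.** **1. Timing.** Inputs: experimental days 10 weeks (70 days) apart; the second after 10 weeks of treatment, taken as about day 71.
- First experimental day: 71 - 70 = about day 1. This is inferred. The text does not give the gap to the first dose, and the schedule figure is not shown.
- Second loss to day 78: 78 - 71 = 7 days. To day 92: 92 - 71 = 21 days.
- If the first loss is near day 1, days 8, 15 and 21 fall about 1, 2 and 3 weeks after it.

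**2. Size of the draw.** 320/500 = 64% of the blood donation that SAFETY uses for comparison. With the VLDL draw a week earlier, 320 + 60 = 380 ml, or 380/500 = 76%.

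**3. Effect on the Epo-placebo gap in hematocrit (simple dilution).** Inputs: 320 ml from SAFETY; hematocrit 45% for placebo and 49% for Epo, borrowed from the earlier study cited there ("Here an increase in hematocrit from 45% to 49% (P <0.05) was found"). Assumptions: blood volume 4.5 to 6.0 L, full plasma refill, no recovery. Fall = hematocrit x volume removed / blood volume.

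| Blood volume | Epo arm (49%) | Placebo arm (45%) | Change in 4-point gap |
|---|---|---|---|
| 4.5 L | 49 x 0.32/4.5 = 3.48 | 45 x 0.32/4.5 = 3.20 | 0.28 (7%) |
| 6.0 L | 49 x 0.32/6.0 = 2.61 | 45 x 0.32/6.0 = 2.40 | 0.21 (5%) |

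The gap becomes 3.72 to 3.79 points. Each arm moves by 2.4 to 3.5 points, but the contrast between arms hardly moves.

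**4. Effect on the tests.** The protocol gives no SD or effect size, so the shift from blood loss alone is an assumption, expressed as d in SDs of the change. The level is 0.05, taken as two-sided because sidedness is not stated.

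Within-group paired t-test, n = 10: the rejection probability comes from the noncentral t with 9 degrees of freedom and noncentrality d x √10.

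| d | Paired test significant, no Epo effect at all |
|---|---|
| 0 | 5.0% |
| 0.25 | 10.9% |
| 0.5 | 29.3% |
| 0.75 | 56.2% |
| 1.0 | 80.3% |

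Epo-versus-placebo t-test on change, 10 against 10, 40,000 simulated trials:
- Same shift in both arms: 5.2% at d = 0.5 and 4.9% at d = 1.0, so the error rate stays at its nominal level.
- Epo arm showing only half the placebo shift: 8.1% at d = 0.5 and 18.4% at d = 1.0.

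**The case against.** The strongest reply is that this is a randomised trial with two placebo groups on the same bleeding schedule. A blood-loss effect common to the arms cancels in the planned group comparison, as steps 3 and 4 show. That stands, and it limits the point to the within-group tests.

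A reader might infer more: that blood loss removes most of the Epo signal, because a fall of 2.6 to 3.5 hematocrit points in the Epo arm looks large beside a 4-point rise. The documents do not support this. The placebo arm loses 2.4 to 3.2 points by the same formula, the calculation allows no recovery over the 21 days to day 92, and all subjects take oral iron. Hematocrit is also not the primary endpoint.

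A reader might also argue that treated men respond differently to the loss, so that cancellation fails. This is possible, and the half-response figures show what it could do. But no passage states or sizes such a difference, and none says how long serum proteins react to a 320 ml loss. It remains a caveat.

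Two further replies have some force. The protocol does not announce a claim on persistence or detection window, so the restriction below is a safeguard and not the correction of a stated claim. And an analysis plan that is not shown may rank the tests. Even so, the protocol lists paired tests beside group comparisons at the same threshold, and its purpose is to find markers of abuse, so a within-arm reading of the day-92 sample is an obvious temptation.

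**Conclusion.** The point holds in a limited form. Within-group paired changes, above all from day 71 to day 92, mix Epo withdrawal with recovery from a loss of about 320 ml. The early change to day 21 does the same for Epo exposure, on condition that the first experimental day lies close to the first dose. The consequence can be material: an assumed shift of 0.5 SD takes a nominal 5% paired test to 29%, and 1.0 SD takes it to 80%. The true shift is unknown.

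The Epo-placebo comparison of change is not confounded by the design itself. Under equal response its error rate stays near 5%, and dilution costs the hematocrit gap only 5-7% under the assumed blood volumes. The documents therefore do not justify rescheduling the experimental days. A gap of, say, 4 weeks before dosing would put the metabolic days about 14 instead of 10 weeks apart and leave an older baseline for the metabolic endpoints.

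**What to change.** 1. In STATISTICS, state that inference on a marker rests on the Epo-versus-placebo difference in change from baseline at days 21, 71 and 92, and that within-group paired tests are descriptive only.
2. In the Serum paragraph of METHODS and in SAFETY, state that the day-78 and day-92 samples follow a blood loss of about 320 ml, by about 7 and 21 days.
3. State that no conclusion on persistence, return to baseline or detection window will be drawn from within-arm washout changes alone. Day 92 is to be read as an Epo-versus-placebo contrast under equal blood loss.

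The cost is wording only: no extra subjects, visits or samples, and no change of schedule. The real downside is that within-arm p-values no longer count as evidence for a marker.

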**Radiation:**

The long-term risks by participating is related to radiation, and can be decomposed as follows: For measurement of glucose turnover radioactive labeled glucose will be infused corresponding to a total of 0.2 mSv and for the determination of FFA turnover the radiation will be 0.4 mSv for the palmitate tracer on each of the experimental days. The infused isotopes for measurement of urea and amino acid metabolism are stable and do not constitute any risk for the participant.

The total amount of radiation the subjects are exposed to on the experimental days is approximately 1.2 mSv., which is somewhat smaller than the radiation they will normally receive during a year (the background radiation is approximately 3 mSv/year) and less than the maximal dose limit (20 mSv per year for workers over 18 years). The DEXA scan is not associated with either pain or discomfort, but is associated with a radiation dose of 0.1 mSv. per scan, which corresponds to 1/30 of the annual background radiation in Denmark and 1/10 of the radiation dose a person would receive from an x-ray of the lungs. One can theoretically calculate the total additional risk of radiation to a 0.014% increase cancer risk during one's lifetime. An average Dane will therefore increase his risk from 25.000% to 25.014%.

**STATISTICS**

Group comparisons will be made with standard statistical methods (t-test and ANOVA or equivalent non-parametric tests). Within the groups, a paired t-test or equivalent non-parametric test will be used. A p-value below 0.05 is regarded as a significant result.

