**SUBJECTS**

A total of 40 healthy young men will be included in the present study. These will be recruited through the web page www.forsøgsperson.dk and various notices on educational institutions in Aarhus (see attached notice).

Because the effect of rHuEpo on some of the required parameters have not previously been elucidated, it has not been possible to make a power calculation. However, from similar studies in our laboratory, it is estimated that approximately 10 subjects in each group is enough to reach statistical power. Furthermore, in a previous study on a group of 8 subjects it was possible to detect significant changes in the proteome 16 days after treatment with rHuEpo (Christensen et al., 2010).

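### Paired within-group tests carry the same p<0.05 rule as the randomised comparisons; effect claims should rest on a baseline-adjusted model with the two crossed factors

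*Protocol*

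**What the plan says.** The DESIGN section describes a randomised study with four arms: "40 subjects in total will be included and randomly assigned to one of the following groups (n = 10"). The arms are placebo or Epo, each with or without endurance training. That is a 2x2 layout with 10 per cell and 20 per level of each factor, although the word factorial is not used.

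The STATISTICS section has three sentences. The first plans the between-group analysis: "Group comparisons will be made with standard statistical methods (t-test and ANOVA or equivalent non-parametric tests"). The second adds the within-group analysis: "Within the groups, a paired t-test or equivalent non-parametric test will be used". The third covers both: "A p-value below 0.05 is regarded as a significant result".

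Three other places matter. Under METHODS, the serum paragraph schedules proteomics at baseline and on days 21, 71 and 92, so a baseline value exists for the primary endpoint. Under SAFETY, iron is given to every arm: "all subjects will be treated with 100 mg iron orally daily from 1 week before the start of the experiment until the end". The same section describes repeated blood sampling for all participants: "Blood loss in total throughout the study will be approximately 850 ml during a 4 months period".

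**The concern.** A paired test in an Epo arm asks whether the marker moved. It does not ask whether Epo moved it. Iron, blood loss and the passage of time act on all four arms and could shift haematological and iron-related serum proteins in every one of them. The third sentence ranks neither kind of test above the other, so a paired p below 0.05 in an Epo arm counts as a significant result just as a randomised comparison does. Finding significance in the Epo arm and not in the placebo arm does not test the difference either. In a study meant to find doping markers, each such result is a potential false candidate.

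The second issue is precision. The effect of physical activity on the markers is a stated aim in the BACKGROUND, so training and the Epo-by-training interaction are both of interest. The section names neither factor and does not use the baseline measurement. With 40 participants, and a SUBJECTS section conceding that "it has not been possible to make a power calculation", precision that costs nothing is worth taking.

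**Working it through.** The protocol gives no power, effect size, SD or baseline correlation, so it has no figure to reproduce.

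**Inputs from the protocol:** 10 per cell, 20 per factor level, significance level 0.05.

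**Assumptions:** two-sided testing; 80% power; a baseline-to-follow-up correlation ρ between 0 and 0.7; a shift common to all arms of 0.25 to 0.75 SD of the change. No multiplicity adjustment across proteins is applied; with one, the absolute detectable effects would be larger.

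**1. Paired test when only a common shift is present.** With no treatment effect and a shift of s (in SDs of the change), the paired t statistic with n=10 is noncentral t on 9 df with noncentrality s√10. Let p be the probability of significance. The arms are independent, so the probability of a significant Epo arm and a non-significant placebo arm is p(1−p).

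| s | s√10 | p | p(1−p) |
|---|---|---|---|
| 0.25 | 0.79 | 0.11 | 0.10 |
| 0.50 | 1.58 | 0.29 | 0.21 |
| 0.75 | 2.37 | 0.56 | 0.25 |

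The nominal value of p is 0.05.

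**2. Bias.** In 20,000 simulated trials with a true Epo effect of 0.80 and a common drift of 0.50, the mean within-group change in the Epo arm was 1.30 (0.80 + 0.50). The 10 vs 10 difference in post values, the 10 vs 10 difference in changes and the baseline-adjusted factorial estimate each averaged 0.80. Their standard deviations were 0.45, 0.45 and 0.28. Only the within-group figure is off target; the between-group methods differ in precision alone.

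**3. Detectable Epo effect, in SDs of the outcome.** The minimum is λ√(2/n), where λ is the noncentrality that gives 80% power.

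- t-test, 10 vs 10 on post values, 18 df: 2.963 × √(2/10) = 1.32.
- Main effect in the 2x2 layout, 20 vs 20, 36 df: 2.879 × √(2/20) = 0.91. The cut is 1 − 0.910/1.325 = 31%.
- The same with a baseline covariate, 35 df: 2.881 × √(2/20) × √(1−ρ²) × √(1+1/35).

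| ρ (assumed) | Adjusted main effect | Cut vs 10 vs 10, post values | Cut vs two-way ANOVA, post values | Cut vs two-way ANOVA, changes |
|---|---|---|---|---|
| 0 | 0.92 | 30% | −1.5% | 28% |
| 0.5 | 0.80 | 40% | 12% | 12% |
| 0.7 | 0.66 | 50% | 27.5% | 6% |

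**4. What the gain does not reach.** The interaction contrast has twice the standard error of a main effect, so at ρ=0.5 its detectable size is 2 × 0.80 = 1.60 SD. For Epo against placebo within one training stratum, the adjusted figure at ρ=0.5 is 1.13 SD against 1.32 SD, a gain of 15%.

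**The case against.** The strongest reply is that the randomised comparison is planned, and planned first. A reader who starts from the sentence on paired tests might infer that the control arms are discarded. The text does not support that: between-group tests come in the preceding sentence, and no passage says that Epo effects will be claimed from paired tests. A reader might also infer that the 2x2 structure is ignored. That is not established, because a two-way ANOVA is an ANOVA and fits the wording. Nor does a baseline-adjusted model remove a bias from the planned group comparisons, because they have none (step 2).

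On size, a cut of a third or more in the detectable effect is tempting to claim but conditional. It needs 10 vs 10 t-tests as the comparator, a main effect as the target and a suitable ρ. At ρ=0 the cut is 30%, and against a two-way ANOVA at ρ=0.5 it is 12%. It is also tempting to say that two arms with the same shift disagree on significance in more than 40% of cases. That counts both directions; the misleading pattern, Epo significant and placebo not, is at most about 25%.

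Finally, whether the ANOVA is one-way or two-way, the response scale and the covariates may properly sit in an analysis plan that is not shown.

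All of this stands, and it limits the point to two parts. The first is not an omission left for later: the protocol itself sets paired significance tests beside the group comparisons under one p-value rule, and an analysis plan that followed that wording would inherit the ambiguity. The second is that the named tests, and especially their usual rank-based equivalents, are a weaker choice than a model using the two randomised factors and a baseline already collected.

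**Conclusion.** The point holds in a limited form. The STATISTICS section lets a within-group p below 0.05 count as a significant result without tying effect claims to the randomised comparison, in a trial where every arm shares iron supplementation and repeated blood sampling. For common shifts of 0.25 to 0.75 SD of the change, the paired test is significant in about 11% to 56% of cases with no treatment effect, and the pattern of Epo significant and placebo not arises in about 10% to 25%. The shift sizes are assumed; the protocol gives no figure for any effect of iron or sampling on serum proteins.

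The between-group tests are valid, and for them the issue is precision only. The detectable Epo main effect falls from 1.32 SD to between 0.92 and 0.66 SD for ρ from 0 to 0.7 if the alternative is 10 vs 10 t-tests on post values. The gain is much smaller if a two-way ANOVA was intended. It applies to main effects; the interaction remains weakly powered.

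**What to change.** In the STATISTICS section, make the primary analysis of each outcome, log-transformed where suitable, a linear model with Epo, training, Epo x training and the baseline value. State that all effect claims rest on its between-group estimates with 95% confidence intervals, and that the pooled Epo effect is read together with the interaction estimate and its interval. Report within-group changes descriptively, without p-values.

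This is a change of wording. It needs no extra participants, samples or visits. It costs one or two degrees of freedom; if baseline turned out to be uncorrelated with follow-up, the loss against a two-way ANOVA on post values would be about 1.5% in the detectable effect.
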